**Other measures**	
Psychosocial parameters	Arthritis Self-Efficacy Questionnaire
	Illness Perception Questionnaire Revised (IPQ-R)
	Medical Outcomes Study (MOS) Social Support Survey
	9-item Patient Health Questionnaire (PHQ-9)
	Revised Health Hardiness Inventory
Physical activity	Physical Activity Scale for the Elderly (PASE)
Use of health care/home assistance and work absences	Log book (retrospectively for prior 4 weeks)
Adverse events	Open-ended questioning (12 weeks)
Treatment session attendance	General practitioner treatment records (12 weeks)

All measures are recorded at baseline, 12 weeks and 12 months unless otherwise stated.

Age, gender, height, weight, duration and nature (unilateral/bilateral) of knee symptoms and previous treatment for knee joint problems were obtained by questionnaire at baseline for descriptive purposes.

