#### Health-related quality of life

Health-related quality of life is measured using the Assessment of Quality of Life instrument version two (AQoL II). The AQoL II has 20 questions that cover six dimensions of health-related quality of life including independent living, social relationships, physical senses, coping, pain and psychological wellbeing. The AQoL has strong psychometric properties and is more responsive than other more widely used scales
[34,35]. It produces a single utility index that ranges from −0.04 (worst possible health-related quality of life) to 1.00 (full health-related quality of life).

The 12-item Short Form Health Survey (SF-12) is also being used to measure health-related quality of life
[36]. The SF-12 is a self-administered questionnaire that was designed to measure patient outcomes in medical practice and clinical research and to evaluate the effectiveness of health interventions. The 12 questions in the SF-12 measure an individual’s perceived health across eight domains: physical functioning; role limitations because of physical health problems; bodily pain; general health perceptions; energy/fatigue; social functioning; role limitations because of emotional problems; and general mental health. The SF-12 is scored so that a high score indicates better functioning. Scoring algorithms are applied to individual item responses to produce the composite Physical Component Summary (PCS) and Mental Component Summary (MCS) scores. The PCS and MCS scores have a range of 0 to 100 and were designed to have a mean score of 50 and a standard deviation of 10; scores greater than 50 represent above average health status.

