### Economic evaluation

The economic evaluation will be conducted from the perspective of the Australian health care system and the individual patient. Standard methods of economic evaluation alongside a clinical trial will be used to evaluate the differences in resource use and health outcomes at the end of treatment and at 12 months. The primary economic evaluation will take the form of a cost effectiveness study with a range of outcome measures including the incremental cost per extra person with a clinically significant improvement in pain and function and per extra quality adjusted life years (QALYs) for laser acupuncture compared to either sham or needle acupuncture. The difference in QALYs will be calculated in the primary analysis as the difference in the area under the curve for AQoL scores over the duration of 12 months. Differences in mean change from baseline for the AQoL to each time point will be weighted by the time from baseline using generalised linear regression modelling adjusting for baseline levels of the AQoL to construct QALYs, and then compared between groups. Differences in the mean cost between groups will be calculated using generalised linear regression modelling. Incremental cost per QALY will be calculated as the ratio of the difference in mean cost to the difference in mean QALYs with 95% confidence intervals calculated using Fieller's theorem.

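### The economic evaluation defines the QALY difference as an area under the AQoL curve, but the weighting rule that follows does not give that area

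*Protocol article*

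**What the plan says.** All the relevant text is in the protocol article.

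- **Definition.** Under Economic evaluation, the QALY difference in the primary analysis is "the difference in the area under the curve for AQoL scores over the duration of 12 months".
- **Construction.** The next sentence reads: "Differences in mean change from baseline for the AQoL to each time point will be weighted by the time from baseline". It continues by naming generalised linear regression, "adjusting for baseline levels of the AQoL to construct QALYs, and then compared between groups".
- **Use.** "Incremental cost per QALY will be calculated as the ratio of the difference in mean cost to the difference in mean QALYs", with a 95% confidence interval by Fieller's theorem.
- **Schedule.** The note to Table 3 says: "All measures are recorded at baseline, 12 weeks and 12 months unless otherwise stated". No exception is stated for the AQoL, so it is measured at 0, 12 weeks and 12 months.
- **Scale.** The AQoL II gives one utility index running from −0.04 to 1.00 (Health-related quality of life).

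The article gives no formula, no numerical weights and no interpolation rule for the QALY.

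**The concern.** An area under a curve weights each measurement by the stretch of time it represents, that is, by the lengths of the intervals on either side of it. The time elapsed since baseline is a different weight. It grows with each later visit, so the 12-month value dominates however little of the year it stands for. Two adjacent sentences therefore prescribe different quantities for the same denominator.

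The difference bears on a question this trial asks. Treatment ends at about 12 weeks. The Background says no studies had reported follow-up beyond three months, and maintenance of effect is one of the trial's aims. The time-from-baseline rule gives too little weight to the end-of-treatment difference and too much to the 12-month one. If it were followed, a benefit that fades would be credited with too few QALYs and a benefit that persists or appears late with too many. Cost per QALY would move the opposite way.

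**Working it through.** The article states no QALY, AQoL effect or cost-per-QALY figure, so there is nothing of its own to reproduce. The check compares the weights that each sentence implies.

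**Inputs**
- Assessment times, from the note to Table 3: 0, t1 = 12/52 = 0.231 year, t2 = 1 year.
- d1 and d2 are the AQoL differences between arms at 12 weeks and 12 months, adjusted for baseline AQoL as the article specifies. The adjusted difference at time 0 is therefore 0.
- The values of d1 and d2 below are assumptions.

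**Area under the curve (trapezoid rule)**

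Area = d1·t1/2 + (d1 + d2)(t2 − t1)/2 = d1·t2/2 + d2·(t2 − t1)/2

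= 0.500·d1 + 0.385·d2.

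In weeks this is 6·d1 + 20·(d1 + d2) = 26·d1 + 20·d2; dividing by 52 gives the same weights.

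**Weighting by time from baseline, as written**

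t1·d1 + t2·d2 = 0.231·d1 + 1.000·d2.

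The week-12 weight is 0.231/0.500 = 0.46 of what the area requires, and the month-12 weight is 1.000/0.385 = 2.6 times it.

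**Illustrative patterns**

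| Pattern | d1 | d2 | Area | As written | Ratio |
|---|---|---|---|---|---|
| Fully faded by 12 months | 0.04 | 0 | 0.0200 | 0.0092 | 0.46 |
| Half-fading | 0.04 | 0.02 | 0.0277 | 0.0292 | 1.06 |
| Sustained | 0.04 | 0.04 | 0.0354 | 0.0492 | 1.39 |
| Late only | 0 | 0.04 | 0.0154 | 0.0400 | 2.60 |

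The two rules agree only when 0.231·d1 + d2 = 0.500·d1 + 0.385·d2, that is, when d2/d1 = 0.269/0.615 = 0.4375.

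**Other readings of the weighting sentence**
- Weights normalised to sum to 1 (0.1875 and 0.8125): ratios to the area are 0.38, 0.86, 1.13 and 2.11 for the four patterns in order.
- Interval-length (step) weights (0.231 and 0.769): 0.46, 0.89, 1.13 and 2.00.

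Neither gives the trapezoid area. Taking t1 as 84/365.25 or 0.25 year leaves the pattern unchanged; at 0.25 the as-written ratios are 0.50, 1.09, 1.43 and 2.67.

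**Effect on cost per QALY**, with an assumed cost difference of 500:
- fully faded: 500/0.0200 = 25,000 by area, against about 54,167 as written;
- half-fading: about 18,056 against 17,105;
- sustained: about 14,130 against 10,156.

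**The case against.** The strongest defence is that the quantity to be estimated is named correctly. The area under the curve is called the primary calculation, standard methods for trial-based economic evaluation are promised, and the weighting sentence says its purpose is to construct QALYs. It can be read as shorthand for time-weighting baseline-adjusted changes to reach the area just named. The literal reading is also implausible: its weights sum to 1.231, so a constant gain of 0.04 held all year would yield 0.0492 QALY, more than the 0.0400 possible. A journal article may leave the exact formula to a fuller plan.

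Most of this stands as to intent, and it rules out the stronger claim a reader might infer, that the cost-per-QALY denominator will be wrong. The text does not show that the literal rule will be used. It does not remove the inconsistency. The article does not leave the weighting open; it states one, and that one does not match its own definition under any of the readings checked.

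A reader might also infer that the rule turns a QALY gain into a loss. It can: with d1 = 0.05 and d2 = −0.02 the area is +0.0173 and the as-written result is −0.0085. But this needs net harm at 12 months after benefit at 12 weeks, and the article gives no basis for expecting that. Near the half-fading pattern the two rules almost coincide.

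**Conclusion.** The point holds as an internal inconsistency of moderate severity. The definition requires weights of 0.500 and 0.385; the construction sentence, carried out as written, gives 0.231 and 1.000. Those weights follow from the visit schedule, baseline adjustment and, for the area, linear interpolation between visits. The size of any error depends on the effect pattern, from 0.46 to 2.6 times the area in the cases tried, and those utility differences are assumed.

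The consequence is conditional on the sentence being followed literally, and it is confined to the cost-per-QALY ratio and its Fieller interval. The cost per extra person with a clinically significant improvement, the pain and function analyses and the sample size do not depend on it.

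**What to change.** Replace the weighting sentence with the trapezoid rule. For each participant, with U0, U12 and U52 the AQoL utilities at baseline, 12 weeks and 12 months, compute

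QALY = (12/52)(U0 + U12)/2 + (40/52)(U12 + U52)/2,

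and regress it on treatment arm and baseline AQoL. With complete data and a linear model using the same covariates throughout, this equals combining the baseline-adjusted differences as 0.500·d1 + 0.385·d2, so either form can be written down.

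The cost is one sentence in the analysis plan. No new data are needed, and because the article describes follow-up as still under way, the wording can be settled before the economic analysis is run.

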### Procedure

Figure 
1 depicts the trial protocol. Eligibility of prospective participants was determined over the telephone by an investigator (MK) not involved in assessment or treatment of participants. Ethical approval was obtained from the University of Melbourne Human Research Ethics Committee (HREC No. 0931840). All participants provided written informed consent. Initially, all participants consented to participate in a longitudinal observational natural history study of chronic knee pain, involving assessments at baseline, 12 weeks and 12 months. All assessments, comprised solely of questionnaires, are completed by participants at home and mailed back to the University of Melbourne, where data is entered by a blinded assessor (MK).

Upon receipt of completed baseline questionnaires, an investigator (KN) accessed the computerised covert randomisation schedule to reveal whether the participant was allocated either (i) laser acupuncture (could be either real laser or sham laser but the investigator and participant are blinded to this information); (ii) needle acupuncture or; (iii) no treatment (control group). Participants randomised into the no treatment arm continue as consented in the natural history observational cohort for the 12 month duration of the study and did not undergo (or are made aware of) any intervention as part of the trial. Participants randomised to receive either laser or needle acupuncture were telephoned by an investigator (KN) and offered the opportunity to undergo the allocated intervention and contribute their data to the trial. Participants allocated to the laser groups were informed they may receive either real laser or sham laser and that this has been randomly pre-determined and would not be revealed to them until the completion of the 12 month assessments. Participants willing to participate in the intervention provided informed consent to do so at this point. Participants who choose not to participate in the intervention continued as initially consented in the natural history observational cohort for 12 months, however their data will be analysed as per intention-to-treat.

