#### Use of health care, home assistance and work absences

Information on health care use (e.g. visits to hospitals, medical practitioners, other health professionals, use of investigative procedures, prescription and non-prescription drugs) and the need for paid and/or unpaid home assistance over the previous four weeks will be collected via a log-book at baseline, 12 weeks and 12 months. Participants are also asked to record any absences from paid employment (if applicable) and/or unpaid work (eg household duties, caring for family/friends) because of their health. The log-book utilises a checklist format to minimize respondent burden and to ensure high quality data is obtained with minimal data loss.

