### Sample size calculations

Our primary endpoints are average overall knee pain measured on a NRS and physical function measured via WOMAC at 12 weeks. The minimum clinically important difference to be detected in OA trials is a change in pain of 1.8 units (on NRS)
[47] and a change of 6 physical function units on the WOMAC (out of 68)
[48]. Calculations are based on an analysis of covariance (ANCOVA) adjusting for baseline of the outcome variable, and assume a between-patient standard deviation of 3.0 units for pain and 12.0 units for WOMAC
[49]. Sample size calculations for our particular study design need to take into account four aspects: clustering effects resulting from treatment of patients by the same therapist for comparisons with the control arm (hypothesis H2); dilution of the treatment effect resulting from the Zelen design
[50]; precision gain from baseline adjustment; and loss to followup. Initially assuming no clustering effects and a regular two-arm parallel RCT design with complete followup, 33 patients per arm would be required to detect the above differences in pain and function with 80% power at a two-sided 5% significance level, using ANCOVA with assumed baseline to 12 week correlations of 0.50 for pain and 0.70 for function
[49]. Adopting a conservative intra-therapist correlation of 0.10 inflates the sample size to 40 patients per arm across a total of 10 therapists. Assuming a conservative 15% non-consent rate for patients randomised to any of the three treatment arms increases the sample size by 1/(1–0.15)^2^ = 38%, and finally, allowing for 15% loss to followup, inflates the total sample size to 66 patients per arm, which we round up to 70 per arm, or 280 patients in total. Assessment of hypotheses H1 and H3 involve within-therapist comparisons only and therefore the precision loss from clustering by therapist does not apply, yielding greater power (90%) for these comparisons.

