### Statistical analyses

The primary analysis of the data will be undertaken using the principle of intention-to-treat with all randomised patients included in the analyses. Demographic and clinical characteristics, as well as baseline data, will be presented to assess the baseline comparability of the intervention groups. Descriptive statistics will be presented for each group as the mean change (standard deviation, 95% confidence intervals) in the outcomes from baseline to each time point. Differences in mean change from baseline to each time point will be compared between groups using random effects linear regression modelling adjusting for baseline levels of the outcome measure and using the treating therapists as random effects to account for clustering of outcomes by therapists. Model assumptions will be checked by standard diagnostic plots. Improvement between acupuncture groups (based on the perceived ratings of change) will be compared using logistic regression with random effects as above and presented as odds ratios with 95% confidence intervals. Multiple imputation methodology will be employed to account for missing data
[51]. No statistical adjustment will be made for multiple testing. All tests will be two sided and carried out at the 5% level of significance.

As part of the secondary analyses of the primary outcomes at 12 weeks and 12 months, we plan to conduct a separate analysis to estimate the effect of treatment in the hypothetical scenario of full adherence to the randomised treatment intervention. Analytical methods for this will utilise instrumental variables methodology involving two stage least squares estimation
[52].

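### The cost model names no baseline covariate, although pre-allocation health-care use is logged and the QALY model is baseline-adjusted: a small, nearly free gain in precision is left unused

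*Protocol article*

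**What the plan says.** Four places in the Protocol article bear on this.

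- **Economic evaluation, QALYs.** Change in AQoL is weighted by time and modelled "using generalised linear regression modelling adjusting for baseline levels of the AQoL to construct QALYs".
- **Economic evaluation, costs.** The next sentence reads "Differences in the mean cost between groups will be calculated using generalised linear regression modelling". No covariate is named. The incremental cost per QALY is then the "ratio of the difference in mean cost to the difference in mean QALYs with 95% confidence intervals calculated using Fieller's theorem".
- **Use of health care, home assistance and work absences.** Health-care use "over the previous four weeks will be collected via a log-book at baseline, 12 weeks and 12 months". Table 3 gives the same recall window: "Log book (retrospectively for prior 4 weeks", closing its bracket there.
- **Procedure.** Only after the completed baseline questionnaires had come back was the schedule opened. An investigator then "accessed the computerised covert randomisation schedule to reveal whether the participant was allocated" to one of the groups.

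For the clinical outcomes, the Statistical analyses section specifies "random effects linear regression modelling adjusting for baseline levels of the outcome measure". The Sample size calculations section lists the gain from baseline adjustment as one of four aspects that the design takes into account.

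**The concern.** The article states baseline adjustment for the clinical outcomes, for the sample size and for QALYs. Cost is also measured at baseline, with the same instrument and recall window as at follow-up, but its comparison is stated without adjustment. Someone who applies the section as written would fit a cost model with treatment group alone.

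What is at stake is precision in the numerator of the cost per QALY, for laser against sham and laser against needle. To the extent that earlier health-care use predicts later use, an unadjusted comparison leaves explainable variation in the standard error of the cost difference. That standard error is one of the components of the Fieller interval.

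**Working it through.** **The article's own figures.** No cost figure is stated, so there is none to reproduce. The sample size can be reproduced, and it uses the same variance factor, 1 − r², that applies here.

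- Pain: 2 × (3.0 × (1.960 + 0.842) / 1.8)² = 43.6. Multiplying by (1 − 0.50²) gives 32.7, so 33 per arm.
- Function: 2 × (12.0 × (1.960 + 0.842) / 6)² = 62.8. Multiplying by (1 − 0.70²) gives 32.02, so 33 per arm.
- Clustering: 1 + (3.3 − 1) × 0.10 = 1.23, and 32.7 × 1.23 = 40.2, against 40 stated.
- Non-consent and loss: 40 / 0.85² = 55.4, so 56. Then 56 / 0.85 = 65.9, so 66, rounded up in the article to 70.

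The article's figures reproduce. They check the method and the number per arm, and say nothing about cost.

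**Inputs for the cost comparison.**

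- 70 per arm and 15% loss (Sample size calculations): 70 × 0.85 = 59.5 evaluable per arm.
- Correlation r between baseline and follow-up cost: not given, so assumed over 0.1 to 0.7. The 0.50 and 0.70 in the article belong to pain and function and cannot be carried over to cost.
- Cost SD: not given, so results are in SD units.

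**Formulae.** The unadjusted standard error is √(2/59.5) = 0.183 SD, and the 95% half-width is 1.96 × 0.183 = 0.36 SD. Linear adjustment for a baseline covariate multiplies both by √(1 − r²). The equivalent number per arm without adjustment is 59.5 / (1 − r²).

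| Assumed r | SE ratio | Cut in SE | 95% half-width (SD) | Equivalent n per arm |
|---|---|---|---|---|
| 0.1 | 0.995 | 0.5% | 0.36 | 60.1 |
| 0.3 | 0.954 | 5% | 0.34 | 65.4 |
| 0.5 | 0.866 | 13% | 0.31 | 79.3 |
| 0.7 | 0.714 | 29% | 0.26 | 116.7 |

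**Skewed costs.** Lognormal costs were simulated with log-scale SD 0.9, 60 per arm and 4,000 replicates, comparing a linear model with and without baseline cost. The ratio of adjusted to unadjusted SE was 0.97, 0.91 and 0.77 at log-scale correlations of 0.3, 0.5 and 0.7. The gain is smaller than in the table because a given correlation of log costs is a weaker correlation of costs. For r = 0.5 on the log scale it is (e^(0.5 × 0.81) − 1) / (e^0.81 − 1) = 0.499 / 1.248 = 0.40, and √(1 − 0.40²) = 0.92, close to the simulated 0.91. Both estimators were unbiased within simulation error.

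**The case against.** The strongest case against the point has four parts.

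1. **Silence is not exclusion.** The article neither states nor rules out covariates in the cost model. A condensed article commonly leaves such a list to the full protocol or an economic analysis plan, and these are not shown. This stands as a limit. The point rests on the contrast with the adjacent QALY sentence, not on proof that adjustment is excluded.
2. **An unadjusted cost comparison is not wrong.** A reader might infer that the cost per QALY is biased, or that chance baseline imbalance does harm beyond the loss of precision. The documents support neither. Randomisation makes the difference unbiased, and its interval already allows for chance imbalance. At r = 0.5 the imbalance carried over has a standard error of 0.5 × 0.183 = 0.092 SD. Its variance, 0.092² = 0.0084, is exactly the 25% of the unadjusted variance (0.25 × 2/59.5 = 0.0084) that adjustment would remove. It is the same loss, and must not be counted twice.
3. **The asymmetry has a reason.** QALYs are built from AQoL change and the area under its curve, so baseline AQoL is part of the outcome itself. Cost in the four weeks before baseline is not part of later cost. Naming a covariate for one model only is therefore not a contradiction. This stands, but it does not remove the available gain.
4. **The gain may be small.** No passage supports a strong correlation, and a four-week window may predict later cost poorly. Sessions vary from 8 to 12, and an assumed 15% decline treatment. If intervention cost is counted, that variation need not follow earlier health-care use. This stands, and it keeps the severity low.

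A reader might also turn the table into power gains. None of hypotheses H1 to H9 concerns cost, and no cost difference, cost SD or power target is stated, so such figures would have no basis in the article.

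**Conclusion.** The point holds as one of efficiency. As worded, the cost comparison passes over a covariate that is measured before allocation is revealed and is already in hand, while the QALY comparison in the same paragraph uses its own. Under linear adjustment with 59.5 evaluable per arm, the standard error of the cost difference would fall by about 0.5% to 29% for assumed correlations of 0.1 to 0.7. At 0.3 or below the fall is about 5% or less, and for skewed costs it is smaller at the same nominal correlation. The interval for the cost per QALY would not narrow by the same percentage, because it also depends on the uncertainty in the QALY difference. Severity is low: the analysis as written is valid, and the full economic plan may already include the adjustment.

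**What to change.** In the Economic evaluation section, after "Differences in the mean cost between groups will be calculated using generalised linear regression modelling", add: adjusting for the cost of health-care use in the four weeks before baseline, taken from the baseline log-book. Use the same adjusted cost difference in every incremental ratio, both per QALY and per extra person improved. If the full economic analysis plan already says this, nothing need change beyond the wording of the summary.

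The cost is small. The baseline log-book has to be costed, and missing baseline entries have to be imputed, for which the multiple imputation named under Statistical analyses can serve. No new data are needed. Naming the covariate before costs are analysed also removes a later choice between adjusted and unadjusted results.

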In recent years there has been a substantial increase in the number of randomised controlled trials (RCTs) investigating the efficacy of needle acupuncture for chronic knee pain. A recent meta-analysis concluded that while placebo-controlled trials show statistically significant benefits for pain, the benefits are small and unlikely to be clinically relevant
[8]. Waiting list-controlled trials however suggest statistically significant and clinically relevant benefits, which may be due to expectation or placebo effects. Accordingly, well-designed rigorous RCTs are needed that control for both placebo and expectation effects in order to evaluate the efficacy of acupuncture for chronic knee pain.

Although acupuncture has been traditionally administered with needles, the use of laser acupuncture has increased because of its pain-free nature and minimal adverse effects
[11]. Laser acupuncture involves the application of low-level laser, which is a form of electromagnetic radiation in the visible or infrared region of the light spectrum. These laser devices are manufactured with such low energy densities that photo-chemical changes are elicited without photo-thermal effects. Within these ranges, various energy levels and wavelengths can be used depending on the tissue penetration required. In laser acupuncture, the beam of light generated is applied to the skin at acupuncture points and/or trigger points, similar to the application of needles.

Laser acupuncture effects are thought to alter peripheral afferent nerve stimulation, modulating spinal cord afferent input on second order neurons and enhancing peripheral endogenous opioid analgesia
[12] as well as acting via centrally mediated mechanisms. Laser also has effects at the local cellular and tissue level
[13] with evidence of modulation of inflammatory processes
[14] varying according to laser dosage
[15].

In contrast to needle acupuncture, the efficacy of laser acupuncture has been less well studied in the management of chronic knee pain. In general, RCTs have used small sample sizes and variable laser dosages in terms of wavelength, total energy, application sites and number of treatments. In a meta-analysis of eight trials published up until 2006 investigating the short-term efficacy (within 4 weeks) of laser therapy for knee OA, statistically and potentially clinically significant pain-relieving benefits over placebo were found

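### Cost-per-QALY uncertainty is to be shown only by Fieller limits, which are finite only if the QALY difference is significant; net monetary benefit should be prespecified alongside

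*Protocol article*

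**What the plan says.** The Economic evaluation section of the protocol article plans a cost-effectiveness study with several outcome measures. One is the incremental cost per QALY for laser acupuncture against sham and against needle. The QALY difference is the difference in area under the AQoL curve over 12 months, adjusted for baseline. The ratio divides the mean cost difference by the mean QALY difference, with "95% confidence intervals calculated using Fieller's theorem". The section gives no other expression of uncertainty for this ratio, and no rule for the case in which the method returns no finite limits.

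The Sample size calculations section concerns only pain and WOMAC function. The authors "assume a between-patient standard deviation of 3.0 units for pain and 12.0 units for WOMAC" and seek "80% power at a two-sided 5% significance level". They arrive at 70 patients per arm. No standard deviation, expected difference or power is given for AQoL or QALYs.

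**The concern.** Fieller's method for a ratio gives a closed interval only when the denominator is clearly different from zero. If the QALY difference is not significant at the 5% level, the 95% set is either the whole real line or everything outside an interval. Nothing in the sample size protects against this, because the denominator was not a sizing outcome.

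The ratio has a second weakness when the QALY difference may be negative. A positive ratio can mean more cost with more benefit, or less cost with less benefit. A negative ratio can mean that laser dominates or that it is dominated. The ratio alone does not separate these cases.

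At stake is how readable one of the trial's main economic results will be. Followed as written, the plan could produce a point estimate with no finite limits and no prespecified alternative.

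**Working it through.** **1. The plan's own sample size.** The inputs are from the Sample size calculations section: target differences of 1.8 (pain) and 6 (function), SDs of 3.0 and 12.0, and "assumed baseline to 12 week correlations of 0.50 for pain and 0.70 for function".

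- Formula: n = 2(1.96 + 0.8416)² · SD²(1 − r²) / d².
- Pain: 2 × 7.849 × 6.75 / 3.24 = 32.7. Function: 2 × 7.849 × 73.44 / 36 = 32.0. The plan states 33.
- Clustering: 33 patients over 10 therapists is 3.3 each, so the design effect is 1 + 2.3 × 0.10 = 1.23 and 33 × 1.23 = 40.6. The plan states 40.
- Non-consent and loss to follow-up: 40 / 0.85² / 0.85 = 65.1. The plan states 66, rounded up to 70.
- Power for H1 and H3 with 70 × 0.85 = 59.5 followed per arm and the effect diluted by 0.85: 89.5% (pain) and 90.1% (function). The plan states 90%.

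The clinical sizing reproduces closely. No corresponding figure for QALYs exists to reproduce.

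**2. When Fieller limits are finite.** Let dE and dC be the estimated QALY and cost differences. The limits R solve A·R² − 2B·R + C = 0, where

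- A = dE² − 1.96² · var(dE)
- B = dC·dE − 1.96² · cov(dC, dE)
- C = dC² − 1.96² · var(dC)

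The set is a closed interval only if A > 0, that is |dE| / SE(dE) > 1.96. The probability of finite limits is therefore the two-sided 5% power of the QALY comparison.

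**3. Size of QALY difference needed.** SD here means the between-patient SD of the 12-month QALY score after baseline adjustment. With 59.5 per arm, SE = SD × √(2/59.5) = 0.183 SD. The observed difference must exceed 1.96 × 0.183 = 0.36 SD (0.33 SD if all 70 are followed).

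**4. Chance of finite limits.** P = Φ(δ/SE − 1.96) + Φ(−δ/SE − 1.96). The true differences δ are assumed.

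| True difference (SD) | 0 | 0.2 | 0.3 | 0.4 | 0.5 | 0.6 |
|---|---|---|---|---|---|---|
| 59.5 per arm | 5% | 19% | 37% | 59% | 78% | 90% |
| 70 per arm | 5% | 22% | 43% | 66% | 84% | 94% |

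In QALY units, with 59.5 per arm and both the SD and the difference assumed:

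| True difference | SD 0.08 | SD 0.12 | SD 0.15 | SD 0.20 |
|---|---|---|---|---|
| 0.02 | 28% | 15% | 11% | 9% |
| 0.04 | 78% | 44% | 31% | 19% |
| 0.06 | 98% | 78% | 59% | 37% |

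**5. Relation to the clinical design effect.** The design effect on pain is 1.8 / (3.0 × √0.75) = 0.69 SD, or 0.59 SD after the 0.85 dilution. If the whole of that carried over to QALYs, finite limits would have about a 90% chance. If 30–50% did (0.18–0.29 SD, assumed), the chance would be about 16–36%.

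**6. Weight of the visits.** With AQoL at 0, 12 and 52 weeks and trapezoids, the QALY difference is 0.50·d(12 weeks) + 0.385·d(52 weeks). A 12-week benefit that has vanished by 12 months enters the QALY difference at half its size.

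**7. Validity of the set.** In 20,000 simulated trials for each of five scenarios (assumed cost difference 300 and cost SD 1500), the Fieller set contained the true ratio in 94.7–95.2% of draws, counting unbounded sets. With QALY SD 0.12 and true difference 0.02, the set was bounded in 14% of draws, the outside of an interval in 27%, and the whole line in 59%.

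**The case against.** The strongest reply is that Fieller's method is correct. Its set keeps 95% coverage, and an unbounded set truthfully reports that the data do not determine the ratio. That stands. Net benefit would not add information; it would show the same uncertainty in a form that can always be reported.

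A second reply is that an article commonly leaves acceptability curves and similar displays to a full economic plan. Their absence alone would be no finding, and that also stands. The point rests on what the article does fix: it names one interval method for the ratio, and that method can return no finite limits.

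Two stronger readings are tempting and should not be drawn.

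- A reader might infer that finite limits are unlikely at this sample size. The documents give no AQoL SD or expected QALY difference, and the chance runs from about 5% to over 90% across assumed inputs. The Background remark that "the benefits are small and unlikely to be clinically relevant" does not settle it. It concerns needle acupuncture against placebo, which is not one of the economic contrasts. For laser, the same section reports larger pain benefits over placebo and suggests that laser may do at least as well as needle.
- A reader might infer that the trial could not answer its cost-effectiveness question. The section also plans cost per extra person with a clinically significant improvement, to which it does not attach Fieller limits. It estimates the cost and QALY differences separately as well, so both components remain available.

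**Conclusion.** The point holds as one about reporting. The stated limits for cost per QALY are finite only when the QALY difference is significant, and the trial was not sized for that comparison. An unbounded set is a real possibility: it is more likely than not for true differences up to about 0.3 SD, and has roughly a 10% chance at 0.6 SD. The boundedness condition is exact. The probabilities rest on assumed true differences, normal estimates, 15% loss to follow-up from 70 per arm and, for the figures in QALY units, assumed SDs. The Fieller method is not invalid and need not be removed. What the plan needs is a companion statistic that is always finite and keeps its sign when the QALY difference is near or below zero.

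**What to change.** Keep the incremental cost per QALY, and report its Fieller limits where they are finite, with a plain statement when they are not. Alongside it, prespecify incremental net monetary benefit for laser against sham and laser against needle: NMB(λ) = λ·dE − dC, with variance λ²·var(dE) + var(dC) − 2λ·cov(dC, dE). Give a regression-based 95% interval over a stated range of willingness to pay λ. Add a cost-effectiveness plane or an acceptability curve from the same data.

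The cost is a little extra programming and the need to state the willingness-to-pay range in advance. No new data are required, and the article describes follow-up as still under way, so this could be set before the economic analysis.
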